## Abstract

**Background.:**

Female genital fistula is a traumatic debilitating injury, frequently caused by prolonged obstructed labor, affecting between 500,000–2 million women in lower-resource settings. Vesicovaginal fistula causes urinary incontinence. Other gynecologic, neurologic and orthopedic morbidity may occur during fistula development. Women with fistula are stigmatized; limit engagement in social, economic, or religious activities; and report high psychiatric morbidity. Improved global surgical access has reduced fistula consequences yet post-repair risks impacting quality of life and well-being include fistula repair breakdown or recurrence and ongoing or changing urine leakage or incontinence. Limited evidence on risk factors contributing to adverse outcomes hinders interventions to mitigate adverse events, protecting health and quality of life after surgery. This study seeks to identify predictors and characteristics of post-repair fistula breakdown and recurrence (Aim 1) and post-repair incontinence (Aim 2), and to identify feasible and acceptable intervention strategies (Aim 3).

**Methods.:**

This mixed-methods study incorporates a prospective cohort study of women with successful vesicovaginal fistula repair at approximately 12 fistula repair centers and affiliated care sites in Uganda (Aims 1–2) followed by qualitative inquiry among key stakeholders (Aim 3). Cohort participants will have a baseline visit at the time of surgery followed by data collection at 2 weeks, 6 weeks, 3 months and quarterly thereafter for 3 years. Primary predictors to be evaluated include patient-related factors, fistula-related factors, fistula repair-related factors, and post-repair behaviors and exposures, collected via structured questionnaire at all data collection points. Clinical exams will be conducted at baseline, 2 weeks post-surgery, and for outcome confirmation at symptom development. Primary outcomes are fistula repair breakdown or fistula recurrence and post-repair incontinence. In-depth interviews will be conducted with cohort participants (n ~ 40) and other key stakeholders (~ 40 including family, peers, community members and clinical/social service providers) to develop feasible and acceptable intervention concepts for adjustment of identified risk factors.

**Discussion.:**

Participant recruitment is underway. This study is expected to identify key predictors that can directly improve fistula repair and post-repair programs and women’s outcomes, optimizing health and quality of life. Furthermore, our study will create a comprehensive longitudinal dataset capable of supporting broad inquiry into post-fistula repair health.

**Trial Registration.:**

ClinicalTrials.gov Identifier: NCT05437939

The evidence base regarding persistent post-repair risks and consequences is underdeveloped, which limits clinical and counseling interventions capable of mitigating harmful processes. Most evaluation has been retrospective. Most previous prospective research on repair failure is limited to the fistula repair hospitalization or early clinical-follow up, with sparse data on predictors of later fistula repair breakdown and recurrence. A study in Guinea reported that women not sexually active at follow-up and those with urethral involvement, damaged bladder neck, and presence of vaginal scarring had significantly higher incidence of fistula recurrence.^14^ Self-reported precursors to fistula recurrence in this study included farm work (19%), walking (12%), sexual intercourse (10%), and pregnancy or childbirth (10%).^14^ In Ethiopia, recurrence was linked to physical strain, sexual intercourse, heavy work, or jostling during transit.^15^ Three smaller studies in Ethiopia, Malawi, and Sudan identified fistula recurrences occurring during a subsequent childbirth.^12,28,29^

Fistula recurrence can be mechanistically characterized as surgical breakdown or re-injury, thus capture of the biological and social factors important to each potential pathway is key. The literature on enhanced recovery after surgery has identified patient counseling, physical conditioning, avoidance of alcohol and smoking, and good nutrition as protective.^30^ Surgical site infection, an intermediate factor associated with late breakdown, is more common among patients with co-morbidities (particularly diabetes), advanced age, risk indices, and lengthier surgery.^31^ Factors responsible for re-injury may include the biological and social structures that increased women’s risk of developing a first fistula, including limited access to emergency obstetric care, and it is possible that a woman’s risk of fistula recurrence following surgery will be different due to the biological alterations occurring within the surgery itself, largely impacted by fistula characteristics which are likely to be important predictors of recurrence outcomes. A small Ethiopian study comparing women with and without persistent post-repair urinary incontinence found that leakage was significantly more likely among younger women at first vaginal birth.^22^

Urinary incontinence following fistula repair is complex due to a variety of anatomic and functional factors at play which often remain uncharacterized, particularly over time.^32–34^ Research on potential intervention points for reducing persistent and incident post-repair incontinence is limited by the breadth of factors assessed, lack of differentiation between incontinence types, and lack of longitudinal follow-up. Predictors of immediate post-repair incontinence include fistula severity, including size and location, presence of vaginal scarring, and shorter urethral length.^11,16,35^ Less is known about incident incontinence following successful surgical resolution.^14,17^

To inform clinical and counseling interventions to optimize women’s health and quality of life following fistula repair, we have developed a mixed-methods research study incorporating a longitudinal cohort to robustly identify predictors of fistula repair breakdown and recurrence (Aim 1), identify predictors and characteristics of post-repair incontinence (Aim 2), supplemented by qualitative work among key stakeholders to identify feasible and acceptable strategies for modifying key risk factors of adverse outcomes (Aim 3). The three proposed specific aims address critical research gaps in the fistula literature and are expected to tangibly inform the development of clinical and counseling interventions to mitigate complications, improve post-surgical outcomes and quality of life. Our investigative approach seeks to elucidate which factors (e.g., patient and fistula characteristics, surgical factors, and post-repair behaviors and exposures) are most important in determining risk of post-surgical adverse outcome, thereby leading to appropriately targeted and contextually-adapted interventions, and will identify priority research areas needed for women with continued poor outcomes.

## Methods

This sequential explanatory mixed-methods study incorporates a longitudinal cohort which will enroll and follow up to 1000 Ugandan women with successfully closed genital fistula from the time of fistula surgery through 36-months post-surgery (quantitative) and in-depth interviews which will be conducted with ~ 80 purposively selected key stakeholders for translation of quantitative findings into feasible and acceptable interventions (Fig. 1). The summarized conceptual framework guiding our study (Fig. 2) highlights factors to be explored including both invariable and potentially mutable factors to develop the evidence base that will allow them to maintain their reproductive and overall health over time.

### Study setting and sites

Our research is situated in Uganda which reports a lifetime fistula symptom prevalence of 19.2 per 1,000 reproductive aged women and ~ 5,000 new cases annually.^36–38^ Uganda’s National Fistula Technical Working Group (est. 2002) with representatives from the Ministry of Health, international and national non-governmental organizations (NGOs), medical professionals, and media has focused on increasing fistula surgery availability; from 2010 to 2015 the annual number of fistula surgeries in Uganda increased from 1377 to 2065.^39^ Fistula surgery is available at 20 centers of excellence in Uganda, with 25 trained surgeons with various levels of experience employed by national and regional referral hospitals. Regional literature suggests that genital fistula repair is successful among ~ 80% of affected women.^18,40^

The research team is partnering with approximately 12 facilities across Uganda providing fistula repair, selected for fistula repair volume, geographic proximity, prior collaboration and research capability (Fig. 3). Various fistula repair models are used across these sites; some sites conduct routine surgeries within ongoing urogynecological services only, others conduct fistula repair camps only, and others combine both routine care and camp models. Patients who are under the care of our study providers and research assistants at alternative inconsistent locations will be considered eligible for study participation if they meet study eligibility criteria.

### Longitudinal cohort study

Our study will recruit a longitudinal cohort of 1,000 women with successful (closed) vesicovaginal fistula repair just after surgery (~ 48 hours later). Participants will be followed for 3 years in total, with data collected via questionnaire at baseline (surgery), 2 weeks (hospital discharge), 6 weeks, 3 months and quarterly thereafter.

#### Study participants.

Inclusion criteria are vesicovaginal fistula, completed fistula surgery with confirmed closure, age 15 or above (where individuals 15–17 meet Ugandan legal criteria for emancipation), and capable and willing to provide informed consent. Exclusion criteria are do not live within a feasible location for follow-up, operationalized by return travel back to fistula repair facility and cellular telephone network.

In the case of fresh fistula, we allow for a special circumstance for study participant inclusion criteria: If limited in size (< 2cm) and time since occurrence (< 3 months), catheterization alone may successfully heal ~ 10% of fistula.^41^ Where a potential participant’s fistula is considered eligible for treatment via catheterization instead of surgery, and the participant undergoes catheterization and is cured (defined as fistula closure, confirmed by methylene blue test), this woman will be considered eligible for study enrollment if she meets all other study eligibility criteria except having undergone surgery.

#### Study procedures.

Local study researchers will recruit participants into the cohort following confirmation of successful fistula repair. Potentially eligible women will be identified through review of urogynecology department surgical logbooks, patient medical records, and via direct communication with fistula surgeons and other providers. After fistula repair, women stay at the repair facility for 14 days at a minimum for post-repair catheterization. The local study researcher will approach women at the facility who meet the eligibility criteria in-person 24–48 hrs after surgery to explain the study to them, assess whether they are eligible and, if so, invite them to participate. The study researcher will complete the full informed consent procedure for those women who indicate that they would like to participate, at a convenient time, with the use of a decision tool developed by the University of California San Francisco Human Subjects Research Ethics Board. The study researcher will then collect participant contact information and administer the baseline questionnaire. Participants will be followed through 36 months post-repair, regardless of outcome.

Two-week data collection will occur prior to hospital discharge. Other planned follow-up data collection (6 weeks and quarterly, starting at 3 months) will occur over mobile phone, given high mobile phone penetration across Uganda.^42,43^ Where women do not have their own phone, the study will provide them with a study phone and phone number. Airtime will be provided throughout the study to ensure that study participants have call time (minutes) available and could pay to charge their phone battery as needed.

Clinical exams will be conducted at baseline and 2 weeks post-surgery for fistula and repair characterization, and as necessary based on women’s self-report of symptom development across the study follow-up to validate outcomes. Participant questionnaires will include a series of signs and symptoms which, if reported, will trigger clinical evaluation at the repair facility for determination of study outcomes: *de novo* urinary or fecal incontinence signifying fistula repair breakdown and recurrence, or any change in urinary incontinence. Women reporting such symptoms on interviewer-administered questionnaire or through other study or clinical communication will return to the fistula repair facility for outcome assessment and clinical care following standard clinical procedures. Clinical assessment is routinely conducted at the in-person follow-up appointments at 6 weeks and 3 months post-repair. Transportation costs will be reimbursed for all follow-up data collection required.

It is possible that some participants may require multiple fistula surgeries during the course of their study participation. If this occurs, participant follow-up will be adjusted to incorporate data collection at 6 weeks and 3 months following the subsequent surgery, after which the regular quarterly data collection will continue through the originally targeted 36 months after the participant’s initial enrollment.

#### Measures.

Primary predictors to be investigated include patient-related factors, fistula-related factors, fistula repair-related factors, and post-repair behaviors and exposures (Table 1), collected via structured questionnaire at all follow-up data collection points and from medical records and clinical forms when examinations are performed. Participant sociodemographic, fistula and fistula-repair characteristics will be measured at baseline, with questions on post-repair behaviors and exposures at each follow-up. Outcomes will be screened for at each data collection point; study interviewers will ask a series of questions on signs and symptoms to identify outcomes of interest, women who report new or changed urinary incontinence will be asked to return to the fistula repair facility for clinical exam to confirm fistula breakdown, recurrence, or incontinence. Women with persistent incontinence without fistula breakdown/recurrence will be asked to respond to a short supplemental questionnaire to characterize this incontinence. Women identified as pregnant will be asked to respond to a short supplemental questionnaire on pregnancy-related exposures and outcomes. We seek to develop a comprehensive longitudinal dataset capable of supporting broad inquiry into health and wellbeing following fistula repair.

#### Data analysis.

To identify predictors of post-repair fistula breakdown and recurrence (Aim 1), we will first calculate the incidence of post-repair fistula breakdown and recurrence and its 95% confidence interval (CIs) overall by dividing the number of events identified by the total person-time observed. The probability of event-free survival at defined time points will be calculated using the Kaplan-Meier estimate. We will then estimate the individual and joint-effects of the patient, fistula, fistula repair, and post-repair characteristics on time to post-repair fistula breakdown and recurrence in order to identify significant factors in time to post-repair fistula breakdown and recurrence. We will fit proportional hazards frailty survival models to jointly analyze times to post-repair fistula breakdown and recurrence.^44^ These models will include a shared frailty at the subject level to accommodate within-subject correlation of times to breakdown and recurrence events and interactions of predictors with event type to accommodate potential differences in the association of predictors with times to the events. These models will also include a shared frailty at the provider level since patients will be clustered within providers within facilities. We will fit the frailty survival models using routines in Stata statistical analysis software.^45^

Prior to fitting multivariable models, we will calculate the estimated correlation of all potential predictors to identify any highly correlated groups of predictors. We will not include such groups of predictors in any multivariable models. We will assess the adequacy of the proportional hazards assumption through inspection of Schoenfield residuals as a function of time. In the event our data violate the proportional hazards assumption, we will modify our modelling approach to accommodate interactions or stratification, as is most appropriate for the data. We will subsequently fit one multivariable proportional hazards regression model to document the comparative relationship between patient, fistula, fistula repair, and post-repair characteristics and the hazard rate of post-repair fistula breakdown and recurrence integrating all independent variables that were associated with the outcome in bivariable analyses at a conservative p threshold of p < 0.1. Final model selection will be determined via Akaike’s Information Criteria.^52^ Secondary analyses will assess time to post-repair fistula breakdown (< 3 months post-repair) and time to fistula recurrence (≥ 3 months post-repair) separately, and by fistula etiology (obstetric versus iatrogenic), although our study is not powered for secondary outcomes.

Other methods will also be used to better understand the contribution of risk factors of fistula repair breakdown and recurrence. To overcome the biases inherent to observational research in understanding causal effects,^46^ we propose conducting a series of secondary analyses employing propensity score methods.^47^ Propensity score methods account for systematic differences in baseline characteristics between exposed and unexposed participants, allowing for effects to be interpreted as causal, similar to a randomized experiment.^48,49^ Indeed, propensity score methods may reduce systematic differences between treatment groups compared to covariate adjustment methods.^47^ For these analyses, we will estimate a series of models for each key modifiable factor to be assessed, first developing models predicting the probability of the particular exposure using key baseline and other measures deemed to be relevant for developing the treatment weight, followed by analyses of the exposure and outcome incorporating the treatment weight to the methods described above. Finally, we will seek to construct a classification rule based on predictors using techniques such as recursive partitioning and random forests using routines in R to identify groups of women defined by the exposure characteristics that have high probability of experiencing the adverse outcome.^50^

To identify predictors and characteristics of post-repair incontinence (Aim 2), we will first estimate the proportion of women who experience post-repair incontinence and the 95% confidence interval at multiple time points (e.g., 6m, 12m, 2y and 3y). Our primary analysis of predictors of persistent post-repair incontinence will focus on incontinence at 3 months, the time point by which incontinence resolvable through surgery will have resolved per expert opinion. We will first estimate bivariable relationships between each predictor and post-repair incontinence at this time point using multi-level mixed effects logistic regression modeling procedures in Stata to accommodate the clustered nature of our data.^51^ Subsequently, we will estimate one multivariable model to understand the independent and joint effects of patient, fistula, fistula repair, and post-repair characteristics on post-repair incontinence at 3m, integrating all independent variables that were associated with the outcome in bivariable analyses at conservative p < 0.1 and addressing correlation as described for Aim 1. To identify predictors of incident post-repair incontinence, we will assess incident post-repair incontinence and factors associated with time to incident post-repair incontinence using the survival analysis methods described for Aim 1. Finally, we will conduct analyses of binary predictors of interest employing propensity scores and seek to develop classification rules following the methods described for Aim 1.

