#### Sample size.

The sample size for our longitudinal cohort study (up to n = 1000 women) was calculated to provide adequate power to detect a minimum difference in effect for patient-related, fistula-related, fistula-repair related, post-repair behaviors and exposures on risk of fistula repair breakdown or recurrence and incontinence of 20% (Aims 1 and 2) using the log-rank test for two-sample comparison of survivor functions (Aim 1) and the Pearson’s chi-squared two-sample proportions test (Aim 2). These effect differences were determined to be clinically significant based on expert opinion.

Power calculations were developed using Stata’s power procedure, with values α = 0.05 and 1-β = 0.80.^51^ Prior research on fistula recurrence risk elsewhere suggests that factors of interest for our survival analyses (Aim 1) may have hazard ratios ranging from 1.0 to 3.4.^14^
Fig. 4 below illustrates the minimum sample size required for estimation of effect estimates ranging from 1.1 to 2.0 with parameters α = 0.05 and 1-β = 0.80, illustrating adequate power for two-sample comparison of survivor functions (i.e., time to fistula repair breakdown, time to fistula recurrence) with a sample size of 1000 for effect estimates (hazard ratios) of 1.2 or higher, illustrating a 20% or higher risk difference, accommodating some loss to follow-up. Research in other locations has reported a repair breakdown or recurrence rate of approximately 15%. With our target sample size of 1000, we anticipate being able to estimate this incidence with a range of precision of approximately 2.5% (i.e., between 12.8%−17.4%).

Sample size calculations for comparisons between risk factors of post-repair urinary incontinence at 6 and 12 months informing this analysis were estimated using the Pearson’s chi-squared two-sample proportions test with parameters α = 0.05 and 1-β = 0.80. The prior literature does not provide a good estimate of what range of potential risk elevation we are likely to see, so we have estimated risk differences of approximately 10 percentage points, across a range of possibilities. As shown in Fig. 4, for a potential comparison of 9 percentage points (e.g., from 1–10%) we achieve power of 0.80 at approximately 200 study participants. On the other end of the range (e.g., a comparison between 50% and 60%; Fig. 6), statistical power of 0.80 is achieved with a minimum sample size of 800 participants.

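### The incidence interval, and the 0.80 power for provider- and facility-level predictors, assume independent women although the protocol describes clustering

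*Protocol article*

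**What the plan says.** In the protocol article, the Data analysis section for the longitudinal cohort adds a provider-level shared frailty to the Aim 1 survival models because "patients will be clustered within providers within facilities". For Aim 2 it chooses multi-level mixed effects logistic regression, also because the data are clustered. The overall incidence of breakdown and recurrence is to be calculated "by dividing the number of events identified by the total person-time observed", with a 95% confidence interval whose variance method is not named.

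The Sample size section uses a two-sample log-rank test for Aim 1 and, for Aim 2, the Pearson chi-squared "two-sample proportions test with parameters α = 0.05 and 1-β = 0.80". For an incidence of 15% in 1000 women it expects a "range of precision of approximately 2.5" percent, with limits of 12.8% and 17.4%. For 50% vs 60% it says that "statistical power of 0.80 is achieved with a minimum sample size of 800 participants". It claims adequate power for all four predictor groups, including the fistula-repair group. It mentions no ICC, design effect or cluster count; the only allowance is an unquantified one for loss to follow-up.

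Study setting and sites gives about 12 partner facilities and 25 trained fistula surgeons in Uganda. Table 1 lists the operating surgeon, the surgeon's level and experience, and the repair center as predictors in the fistula-repair group.

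**The concern.** The two sections describe different data. One treats women operated on by the same provider as correlated; the other computes precision and power as if they were not.

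Two statements are affected. The first is the interval around 15%, because the variance of an overall rate is inflated by positive correlation within providers or facilities. The second is the adequate-power statement as it applies to provider and facility characteristics. For those, the information comes mainly from the number of providers or sites rather than from 1000 women. A null result for surgeon experience or repair center could then be read as coming from an adequately powered comparison when it did not.

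**Working it through.** **Inputs from the protocol article.** N = 1000; incidence 15%, so 150 events; α = 0.05 and power 0.80; 50% vs 60% at N = 800; 1% vs 10% at about N = 200; about 12 facilities. Two-sided testing is not stated, but it reproduces the figures.

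**Assumptions.** ICC 0.01–0.05, since none is given. Equal cluster sizes. 25 providers, which is the national count of trained surgeons used as a working number. Cluster size m is 1000/25 = 40 or 1000/12 = 83.3.

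**1. Reproducing the stated figures with independent women**
- Exact binomial interval for 150/1000: 12.84%–17.37%, which matches 12.8%–17.4%. Wald gives 12.8–17.2% and Wilson 12.9–17.3%.
- 50% vs 60%: 388 per group, 776 in total (816 with continuity correction). N = 800 gives power 0.81.
- 1% vs 10%: 100 per group, 200 in total.

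All of these match with a design effect of 1, so none contains an allowance for clustering.

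**2. Interval with clustering**

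DE = 1 + (m − 1) × ICC; effective n = 1000/DE; exact interval for 15% at the effective n.

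| Clusters | ICC | DE | Effective n | Interval for 15% |
|---|---|---|---|---|
| 25 providers | 0.01 | 1 + 39 × 0.01 = 1.39 | 719 | 12.5–17.8% |
| 25 providers | 0.02 | 1.78 | 562 | 12.1–18.2% |
| 25 providers | 0.05 | 2.95 | 339 | 11.4–19.3% |
| 12 facilities | 0.01 | 1 + 82.3 × 0.01 = 1.82 | 548 | 12.1–18.3% |
| 12 facilities | 0.02 | 2.65 | 378 | 11.6–19.0% |
| 12 facilities | 0.05 | 5.12 | 195 | 10.3–20.8% |

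**3. Power for a predictor fixed within the cluster, 50% vs 60%, all 1000 women, equal groups**

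With n = 500/DE per group, power = Φ{[0.10√n − 1.96√(2 × 0.55 × 0.45)] / √(0.25 + 0.24)}.

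- Independent women, n = 500: (2.236 − 1.379)/0.700 = 1.22, so power is 0.89.
- 25 providers, ICC 0.01, 0.02, 0.05: 0.77, 0.66, 0.46.
- 12 facilities, same ICCs: 0.65, 0.50, 0.29.

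At the stated minimum of 800 women (m = 32 or 66.7), power for ICC 0.01 to 0.05 is 0.70 to 0.43 with 25 providers and 0.60 to 0.28 with 12 facilities. The formula uses a normal reference distribution with no correction for few clusters, so these values are, if anything, generous.

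**4. Slack at N = 1000.** For 50% vs 60%, power stays at 0.80 up to DE = 1000/776 = 1.29. That corresponds to ICC 0.29/39 ≈ 0.007 with 25 providers and 0.29/82.3 ≈ 0.0035 with 12 facilities. For 1% vs 10% the tolerated design effect is 1000/200 = 5.

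**5. Woman-level predictors.** A simulation used 12 clusters, N about 800, 50% vs 60% and outcome ICC 0–0.05, comparing exposed and unexposed women within clusters.
- Exposure spread evenly over clusters: power 0.81–0.82, so no loss.
- Latent exposure ICC 0.1: 0.78–0.79.
- Latent exposure ICC 0.3: 0.71–0.73.
- Latent exposure ICC 0.6: 0.58–0.60.

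The within-cluster comparison discards between-cluster information, so a mixed model would lose somewhat less in the last three cases.

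**The case against.** **Most predictors are unaffected.** A reader might infer that the 0.80 power is overstated throughout. The documents do not support that. Nearly all Table 1 predictors are measured on the individual woman, and the planned mixed and frailty models compare such exposures within clusters with little or no loss. The target of 1000 also exceeds the 800 and 200 quoted for Aim 2. This stands, and it confines the power point to predictors set by provider or site, or strongly concentrated there.

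**The size is assumed.** No ICC is given. The 25 surgeons are a national count, not a cap on study providers, and some patients may be treated at other locations. At ICC 0.005 with 25 providers the interval is 12.6–17.6%, so a precision of about 2.5 points roughly holds. This also stands: the direction is certain for any positive ICC, but the size is not.

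**Sites as fixed strata.** The facilities were chosen for volume, proximity, prior collaboration and research capability. If inference is confined to these sites, variation between them need not widen the interval as the 12-facility rows show. That is a fair reason not to rest on the extreme row. It does not remove the provider level, which the plan itself models as a random effect.

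**Silence on the incidence variance.** The quoted words define the point estimate; no variance method is named. A reader might infer that the plan has chosen an interval that ignores clustering, but the text does not say so, and an analysis plan may settle it. What can be criticised is the printed 12.8%–17.4%, which does ignore it.

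**Conclusion.** The point holds in limited form. The stated interval of 12.8%–17.4% and the stated power figures assume independent women, against the article's own description of its data.

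- **Interval:** too narrow for any positive ICC. Under an assumed ICC of 0.01–0.05 it is about 12.5–17.8% to 11.4–19.3% (25 providers) or 12.1–18.3% to 10.3–20.8% (12 facilities).
- **Power:** too favourable for the operating surgeon, surgeon level and experience, repair center, and exposures strongly concentrated by site. For 50% vs 60% with all 1000 women it is about 0.77–0.46 at provider level and 0.65–0.29 at facility level. Evenly spread woman-level predictors keep their power.

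These sizes rest on the assumed ICC, equal clusters and the working number of providers. Figure 4 is not shown, so its inputs could not be checked.

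A reader might also infer that a design effect would put the Aim 1 claim of a hazard ratio of 1.2 at N = 1000 in order. It would not. That effect needs about 945 events, while 15% of 1000 gives about 150, so power is about 0.20 even with independent women. That error is separate and larger.

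**What to change.** In the Sample size section:
- Restate the interval for 15% and the power with an explicit assumed ICC range, about 12 facilities and the expected number of study providers.
- Limit the adequate-power statement to woman-level predictors that vary within provider and facility.
- Give a separate minimum detectable effect for provider- and facility-level predictors.

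In the Data analysis section, specify that the overall incidence interval uses a variance that allows for clustering, with a small-sample correction because clusters are few.

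The cost is some wording and one recalculation. The stated figures become less favourable. No change in enrolment is needed for this point. The Aim 1 event count needs its own correction, which this change does not supply.
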